### Intervention

The crowdsourcing intervention is composed of two parts: 1) promotional materials developed through a nation-wide open contest in China, 2) a series of mini crowdsourcing contests to solicit participant feedback to improve the promotional materials. The impact of crowdsourcing is expected through both receiving the crowdsourced messages and actively engaging with the message.

Upon enrollment, participants will be required to add the designated study account as a WeChat contact. The study account will be monitored and maintained by the researchers. The intervention materials—two videos and two images designed to increase awareness about HCV—will be delivered to participants over the course of 2 weeks as individual messages. The initial materials were developed through a nation-wide open contest in China, and was previously evaluated for hepatitis testing uptake in men-who-have-sex-with-men (MSM) in China [15].

Next, participants will be asked whether they have expertise in the following fields: healthcare, social media, or education. Participants who have expertise will be asked to reflect on the intervention based on their expertise, while participants without expertise will be encouraged to reflect based on personal experience. All participants will be invited to submit 50- to 200-character suggestion on how to improve the intervention materials. Submissions will be judged by a panel of health workers, researchers, and community advocates on the following: [1] potential to encourage HCV testing [2]; creativity [3]; potential to engage social media users; and [4] feasibility in clinical settings in Shenzhen. Suggestions for improvement will be shared anonymously among agreeable participants who are receptive to receive frequent updates from WeChat. Top scoring suggestions that meet the predesignated standard will receive cash prizes up to 500 Chinese yuan (72.5 USD). Feasible suggestions will be incorporated into the intervention materials and presented to the next round of participants.

Participants in the control arm will only receive the baseline and follow-up surveys via WeChat. They will not receive any promotional materials as there are currently no materials used in standard-of-care HCV testing promotion at the hospital. In the final week of the intervention period, all participants will receive a reminder to obtain HCV testing and a follow-up survey.

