**Methods:**

A randomized controlled, two-armed trial (RCT) is being conducted in Shenzhen with 1006 participants recruited from primary care sectors of The University of Hong Kong-Shenzhen Hospital. Eligible participants are ≥30 years old; a resident in Shenzhen for at least one month after recruitment; no screening for HCV within the past 12 months and not known to have chronic HCV; and, having a WeChat social media account. Allocation is 1:1. Both groups will be administered a baseline and a follow-up survey (4-week post-enrollment). The intervention group will receive crowdsourcing materials to promote HCV testing once a week for two weeks and feedback will be collected thereafter, while the control group will receive no promotional materials. Feedback collected will be judged by a panel and selected to be implemented to improve the intervention continuously.

Those identified positive for HCV antibodies will be referred to gastroenterologists for confirmation and treatment. The primary outcome will be confirmed HCV testing uptake, and secondary outcomes include HCV confirmatory testing and initiation of HCV treatment with follow-ups with specialist providers. Data will be collected on Survey Star^@^ via mobile devices.

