## Methods

### Study design

This study will include: a pilot study to test the feasibility of participant recruitment in a tertiary hospital in Shenzhen and the social media-based intervention delivered on smartphones; a randomized controlled trial (RCT) to investigate the effectiveness of a crowdsourced intervention compared to no intervention (standard-of-care) in increasing HCV test uptake and linkage-to-care i.e. patients found to be positive for HCV will be referred onto the Division of Gastroenterology of HKU-SZH for further management, if agreeable to the patients.

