#### Linkage-to-care for HCV at HKU-SZH

During the four-week intervention period, participants tested positive for HCV antibody screening test will be referred to Department of Gastroenterology at the hospital. Blood tests will be collected for HCV confirmatory testing, and the participant will be informed of the test results within five working days. Those who have confirmed HCV infection via HCV RNA testing (Abbott Laboratories, lower limit of detection 15 IU/mL), respectively, will be referred to HKU-SZH’s specialty Liver Clinic in the Department of Gastroenterology for further diagnostic workup (liver biochemistry, ultrasonography, transient elastography, genotyping) and discussion of direct-acting antiviral treatment. Sovaldi-based treatment will be discussed, which will be replaced by Epclusa-based treatment when available. Patients will then be monitor for sustained virological response. After successful eradication, patients with cirrhosis or advanced fibrosis will continue follow-up at the HKU-SZH Liver Clinic, while those with non-advanced fibrosis will be referred to FMPC for follow-up. Participants that obtain anti-HCV testing or HCV RNA confirmatory testing at any facility in Shenzhen will be reimbursed for testing costs if they are able to provide medical records for confirmation.

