### Outcomes

The primary outcome is the number of anti-HCV screening tests completed by participants in either RCT arm within 4 weeks after enrollment. This dichotomous outcome will be determined by a single endpoint: uptake of HCV antibody screening test. Participants will only be counted as achieving the primary outcome if medical records at HKU-SZH or in another facility in Shenzhen confirm that they had tested for HCV during the intervention period. Medical records would be assessed based on either the administrative record or photo verification of official testing record.

Secondary outcomes are as follows: rate of participation in the crowdsourcing intervention; content of feedback submissions; number of participants that self-report HCV antibody testing but are not confirmed by medical records; number of participants that follow-up for HCV confirmatory testing; number of HCV diagnosed participants to continue with anti-HCV treatment, versus those who decline treatment for any reason; number of participants that will be completely cured of HCV infection, versus number that drop out prior to completing treatment; number of participants diagnosed with chronic liver disease (including cirrhosis, liver failure, or hepatocellular carcinoma); number of participants that will return to primary care for chronic liver disease follow-up or future screening of HCV and other conditions. Definitions for all study outcomes are provided in Table 1.

**Table 1 Tab1:** Primary and secondary outcomes with definitions

**Primary Outcome**	**Definition**
Confirmed HCV testing uptake	Participants that complete HCV testing as confirmed by medical records at HKU-SZH or other public facility in Shenzhen within 4 weeks of enrollment
**Secondary Outcomes**	**Definitions**
Self-reported HCV testing uptake	Participants that complete HCV testing within 4 weeks of enrollment, self-reported in follow-up survey
Followed-up for HCV confirmatory testing	Participants that follow-up with a provider at HKU-SZH for HCV RNA diagnostic testing, as confirmed by medical records at HKU-SZH or other public facility in Shenzhen
Self-reported follow-up for HCV confirmatory testing	Participants that follow-up with a provider at HKU-SZH or other care facilities in China for HCV RNA confirmatory testing, self-reported in follow-up survey

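### Controls are sent a testing reminder inside the primary outcome window, so the comparator is surveys plus reminder plus reimbursed testing, not no intervention or standard of care

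*Protocol article*

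**What the plan says.** All references are to the protocol article.

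- **Study design** describes the trial as testing the crowdsourced intervention "compared to no intervention (standard-of-care) in increasing HCV test uptake and linkage-to-care". **Primary analysis** likewise frames the question as superiority to standard of care.
- **Intervention** says of the comparator: "Participants in the control arm will only receive the baseline and follow-up surveys via WeChat". It adds that controls get no promotional materials because the hospital uses none in its usual HCV testing promotion.
- The same paragraph then says that, in the last week of the period, "all participants will receive a reminder to obtain HCV testing and a follow-up survey".
- **Linkage-to-care** gives the length of the period: "During the four-week intervention period".
- **Outcomes** defines the primary endpoint: "The primary outcome is the number of anti-HCV screening tests completed by participants in either RCT arm within 4 weeks after enrollment". A test counts if medical records confirm it. No rule sets aside tests taken after the reminder.
- **Incentives and compensation** reimburses the antibody test in either arm, up to 28 RMB, provided the test date lies within the intervention period.

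**The concern.** A direct message telling someone to get tested is a form of testing promotion. Sending it to controls contradicts the statement that they receive surveys alone. It also contradicts the label of no intervention, because the protocol does not present such a message as part of usual care.

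What is at stake is the conclusion. Readers of the result will take the arm difference as the effect of crowdsourcing over what patients would ordinarily receive. The design instead measures what crowdsourcing adds for people who are all reminded, all surveyed and all offered reimbursement. A small or null difference could then be misread as failure against standard care. The planned 10-point difference may also be harder to reach, because controls have more untested people for a reminder to move.

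**Working it through.** **Step 1: is the reminder inside the outcome window?** The intervention period is four weeks (Linkage-to-care), so its last week is roughly days 22 to 28. The primary outcome runs to four weeks after enrolment (Outcomes). The reminder therefore precedes the close of the window. If the period were instead read as the two weeks over which materials are delivered, the reminder would come earlier and still fall inside the window.

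**Step 2: what does each arm receive?**

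| Element | Intervention | Control |
|---|---|---|
| Baseline and follow-up surveys | yes | yes |
| Reminder to test | yes | yes |
| Reimbursed test | yes | yes |
| Crowdsourced materials and feedback contests | yes | no |

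The arms differ only in the last row. The contrast is crowdsourcing on top of the shared elements against the shared elements alone.

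**Step 3: reproduce the plan's sample size.** Inputs from Sample size: 35% v 45% (the 10% improvement read as percentage points), 90% power, alpha 5%. Two-sided testing is assumed, because the text does not state it. With pooled variance under the null and no continuity correction,

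n per arm = [1.960 × √(2 × 0.40 × 0.60) + 1.2816 × √(0.35 × 0.65 + 0.45 × 0.55)]² / 0.10²

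= [1.358 + 0.883]² / 0.01 ≈ 502.3, rounded up to 503, or 1006 in total. This matches the plan. Power at 503 per arm is 90.0%.

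**Step 4: sensitivity to a shared reminder.** The documents give no reminder effect, so everything here is an assumption. Take 35% and 45% as the rates without the reminder, and let the reminder convert the same fraction f of the untested in each arm:

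- control = 0.35 + 0.65f
- intervention = 0.45 + 0.55f
- difference = 0.10 × (1 − f)

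| f | Control | Intervention | Difference (points) | Power at 503 per arm | Total N for 90% power |
|---|---|---|---|---|---|
| 0 | 35.0% | 45.0% | 10.0 | 90% | 1006 |
| 5% | 38.25% | 47.75% | 9.5 | 86% | 1138 |
| 10% | 41.5% | 50.5% | 9.0 | 82% | 1286 |
| 20% | 48.0% | 56.0% | 8.0 | 72% | 1636 |
| 30% | 54.5% | 61.5% | 7.0 | 61% | 2086 |

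**Step 5: the alternative reading of the planning rates.** Sample size takes the 35% from conventional public health messaging, that is, from people already prompted to test. If 35% v 45% are read as final four-week rates with the reminder included, nothing is added and power remains 90%.

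**The case against.** **The comparison is not biased.** This stands. The reminder is the same in both randomised arms, so the estimate is valid for crowdsourcing added to shared procedures. Any dilution works against a superiority claim. A shared reminder is a legitimate design choice, and the protocol discloses it in the paragraph that describes the control. None of this makes the comparator label correct.

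**A reader might infer that the trial is underpowered, at 61% to 82%.** The documents do not support that as a finding. It needs a reminder effect that they do not give, equal in both arms, stacked on a 35% rate that already comes from prompted people and so may count prompting twice. Starting rates matter too. The Background cites 14.3% v 37.5% from 100 people in an HBV study. With f = 30% this becomes 40.0% v 56.2%, and power is still above 99%. With a 14.3% control rate and the planned 10 points, power is 89% at f = 10%, 76% at 20% and 61% at 30%. The materials could also make intervention participants more responsive to the reminder, which would offset the dilution.

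**A reader might infer that the follow-up survey goes out early and cuts short the self-reported four-week outcome.** The Abstract places the survey at four weeks, and the last week of the period includes day 28, so the two statements are compatible. The text does not say that the survey goes out early in that week. The primary outcome rests on records in any case.

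**Moving the reminder after the window is not a clean remedy.** This also stands. It would urge people to take a test outside the dates on which Incentives and compensation allows reimbursement.

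**Conclusion.** The description of the comparator is wrong as written. The Intervention section contradicts itself, and the control condition is surveys plus a testing reminder plus reimbursed testing. This follows from the text alone and needs no assumption.

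Randomisation and the validity of the comparison are intact. What changes is the question answered, and so what the trial may conclude: crowdsourcing added to a reminder against the reminder alone.

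A narrower risk difference is the expected direction if the reminder works about equally in both arms, but its size cannot be derived. The range runs from no loss (power 90%, if the planning rates already include the reminder) to a difference of 7.0 points and 61% power (if they do not, and the reminder converts 30% of the untested). These figures are a sensitivity range, not an estimate, and the sample size arithmetic itself is correct.

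**What to change.** 1. In Intervention, reconcile the sentence limiting controls to surveys with the one sending everyone a reminder.
2. In Study design, Intervention, Primary analysis and the eventual conclusions, describe the comparator as surveys plus testing reminder plus reimbursed testing. State the effect as crowdsourcing added to these elements.
3. Keep the four-week confirmed count as the primary outcome. Prespecify, as a key supportive analysis, confirmed tests dated before the reminder is sent, with the reminder scheduled the same number of days after enrolment in both arms. This contrast is free of the reminder, though surveys and reimbursement remain common to both arms.

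The cost is small. Test dates are already verified for reimbursement, so no new data are needed. The sponsor accepts a less favourable description of the contrast and one extra analysis over a window about a week shorter.

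If the sponsor prefers to send the reminder after the window closes, the rule that reimbursed tests must fall within the intervention period has to be reconciled with that change.

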#### Linkage-to-care for HCV at HKU-SZH

During the four-week intervention period, participants tested positive for HCV antibody screening test will be referred to Department of Gastroenterology at the hospital. Blood tests will be collected for HCV confirmatory testing, and the participant will be informed of the test results within five working days. Those who have confirmed HCV infection via HCV RNA testing (Abbott Laboratories, lower limit of detection 15 IU/mL), respectively, will be referred to HKU-SZH’s specialty Liver Clinic in the Department of Gastroenterology for further diagnostic workup (liver biochemistry, ultrasonography, transient elastography, genotyping) and discussion of direct-acting antiviral treatment. Sovaldi-based treatment will be discussed, which will be replaced by Epclusa-based treatment when available. Patients will then be monitor for sustained virological response. After successful eradication, patients with cirrhosis or advanced fibrosis will continue follow-up at the HKU-SZH Liver Clinic, while those with non-advanced fibrosis will be referred to FMPC for follow-up. Participants that obtain anti-HCV testing or HCV RNA confirmatory testing at any facility in Shenzhen will be reimbursed for testing costs if they are able to provide medical records for confirmation.

#### Pilot study

Thirty participants will be recruited for the pilot to evaluate on the feasibility intervention delivery via WeChat and the participatory and iterative components of the intervention package. In addition, the pilot will inform the expected rate of recruitment, rate of participant retention from completion of the baseline survey to HCV testing uptake, and rate of linkage-to-care. At the end of the pilot period, participants will be asked to provide feedback on the trial design.

### Outcomes

The primary outcome is the number of anti-HCV screening tests completed by participants in either RCT arm within 4 weeks after enrollment. This dichotomous outcome will be determined by a single endpoint: uptake of HCV antibody screening test. Participants will only be counted as achieving the primary outcome if medical records at HKU-SZH or in another facility in Shenzhen confirm that they had tested for HCV during the intervention period. Medical records would be assessed based on either the administrative record or photo verification of official testing record.

Secondary outcomes are as follows: rate of participation in the crowdsourcing intervention; content of feedback submissions; number of participants that self-report HCV antibody testing but are not confirmed by medical records; number of participants that follow-up for HCV confirmatory testing; number of HCV diagnosed participants to continue with anti-HCV treatment, versus those who decline treatment for any reason; number of participants that will be completely cured of HCV infection, versus number that drop out prior to completing treatment; number of participants diagnosed with chronic liver disease (including cirrhosis, liver failure, or hepatocellular carcinoma); number of participants that will return to primary care for chronic liver disease follow-up or future screening of HCV and other conditions. Definitions for all study outcomes are provided in Table 1.

**Table 1 Tab1:** Primary and secondary outcomes with definitions

**Primary Outcome**	**Definition**
Confirmed HCV testing uptake	Participants that complete HCV testing as confirmed by medical records at HKU-SZH or other public facility in Shenzhen within 4 weeks of enrollment
**Secondary Outcomes**	**Definitions**
Self-reported HCV testing uptake	Participants that complete HCV testing within 4 weeks of enrollment, self-reported in follow-up survey
Followed-up for HCV confirmatory testing	Participants that follow-up with a provider at HKU-SZH for HCV RNA diagnostic testing, as confirmed by medical records at HKU-SZH or other public facility in Shenzhen
Self-reported follow-up for HCV confirmatory testing	Participants that follow-up with a provider at HKU-SZH or other care facilities in China for HCV RNA confirmatory testing, self-reported in follow-up survey
Initiated anti-HCV treatment	Participants that have a confirmed HCV diagnosis and initiate anti-HCV treatment at HKU-SZH Department of Gastroenterology, confirmed by medical records at HKU-SZH or other public facility in Shenzhen
Completed anti-HCV treatment	Participants that complete the full anti-HCV regiment, as confirmed by medical records at HKU-SZH
Diagnosed with chronic liver disease	Participants that are diagnosed with chronic liver disease including cirrhosis, advanced cirrhosis, or hepatocellular carcinoma at any point during the study, as confirmed by medical records at HKU-SZH
Followed-up with Liver Clinic for advanced chronic liver disease	Participants that are diagnosed with advanced chronic liver disease (i.e. advanced cirrhosis) and receive follow-up care at the Liver Clinic at HKU-SZH, as confirmed by medical records at HKU-SZH
Cured of HCV infection	Participants that achieve sustained virological response (SVR), defined as absence of detectable hepatitis C virus 12 weeks after completion of treatment, confirmed by medical records at HKU-SZH
Returned to primary care for future screening	Participants that returned to FMPC for services including regular HBV/HCV screening, HBV screening, HIV screening, other STI screening, as confirmed by medical records at HKU-SZH

### Data collection and measures

Pre-intervention and post-intervention surveys will be delivered to the participants’ mobile devices and completed using Survey Star^@^ (Wechat, China), a web-based survey platform that meets industry standards for security and functionality. Both surveys were written in Chinese and verified for clarity and cultural appropriateness with 13 Chinese individuals in Guangdong province, including both genders and ages groups.

Recruited individuals will first be assessed for eligibility by the researcher. Eligible participants will then be asked to complete the baseline survey on Survey Star^@^. The baseline survey will include the following domains: sociodemographic characteristics, including migrant status; access to healthcare at HKU-SZH; trust in healthcare providers; knowledge of and attitudes towards HCV; and risk of contracting HCV. Migrant status will be defined based on the definition of internal migrant from the National Bureau of Statistics of China [23]. Trust in healthcare providers will be assessed using three items previously used to measure provider trust in young Chinese men [15]. Stigma towards HCV will be assessed using a combination of items adapted from the Toronto. Risk of contracting HCV was assessed using 8 items typically used by HKU-SZH providers for assessing HCV risk.

### Confidentiality

Baseline and follow-up survey data will be collected on Survey Star^@^. For follow-up on HCV testing results at HKU-SZH or in one of the connected public hospitals in Shenzhen, patient records in the electronic medical system will be traced by the research team using self-reported hospital registration ID and demographic information. All study data will be encrypted prior to transmission and will be stored in a secure server and can be access by login information known only to the research team. Ethics approval is obtained through the IRB of HKU-SZH (hkuszh201888).

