### Recruitment

Recruitment will continue until 1006 eligible subjects are enrolled. The primary recruitment sites will be FMPC clinic rooms, as well as the endoscopy suite of HKU-SZH, which performs 22,000 endoscopies per year. Patients will be recruited by physicians during their clinic or endoscopy suite visit. HCV screening at endoscopy suites in the United States has been shown to increase HCV testing uptake by threefold [18]. In China, there is evidence that the reported prevalence of HCV increases with age, and individuals above the age of 30 years have seen an increase in reported incidence from passive HCV detection [19].

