### Eligibility criteria

Prior to enrollment, potential participants must first complete an informed consent form in Chinese language, which explains the purpose of the study as well as the rights and responsibilities of the subject participants. Participants are invited to participate if they are 30 years old or older, have Chinese nationality, and will reside in Shenzhen for the following month. Participants will be excluded if they self-report one of the followings: known chronic HCV infection, testing for serum anti-HCV in the past 12 months, current or planned pregnancy, currently undergoing complex medical treatment for other conditions. All eligible participants must provide a working unique mobile phone number and a WeChat account to be enrolled. Wechat is currently the most popular messaging social media app in China, with more than 1 billion active users and 45 billion daily text messages according to the statistics shown in [20].

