### Monitoring

A researcher will check each survey for completion and internal consistency. Each participant’s baseline and follow-up survey and test report will be checked for consistency of their verified cell phone number and demographic information. Test results must be confirmed by testing records at HKU-SZH or verified based on participant socio-demographics as reported in their baseline survey. A telephone number and WeChat account managed by the research team will be made available to participants for any questions or concerns that may come up during the study.

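### The record-confirmed primary outcome is traced with a self-reported hospital ID, although recruitment happens at hospital visits where the ID could be taken from the visit record

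*Protocol article*

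**What the plan says.** Four places in the protocol article determine how the primary outcome is ascertained.

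- **Recruitment:** "Patients will be recruited by physicians during their clinic or endoscopy suite visit". The sites are described as follows: "The primary recruitment sites will be FMPC clinic rooms, as well as the endoscopy suite of HKU-SZH".
- **Eligibility criteria:** "All eligible participants must provide a working unique mobile phone number and a WeChat account to be enrolled". A hospital registration number is not among the items named there.
- **Outcomes:** "Participants will only be counted as achieving the primary outcome if medical records at HKU-SZH or in another facility in Shenzhen confirm" a test in the intervention period. On the form of proof: "Medical records would be assessed based on either the administrative record or photo verification of official testing record".
- **Confidentiality:** for tests at HKU-SZH or a connected public hospital in Shenzhen, "patient records in the electronic medical system will be traced by the research team using self-reported hospital registration ID and demographic information".

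The Monitoring section adds checks: "Test results must be confirmed by testing records at HKU-SZH or verified based on participant socio-demographics as reported in their baseline survey". It also says that each participant's surveys and "test report will be checked for consistency of their verified cell phone number and demographic information". Under Incentives and compensation, the test cost is reimbursed in both arms, up to 28 RMB, once the follow-up survey is complete and the record is confirmed. The data analysis section and the missing data plan both include participants lost to follow-up.

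**The concern.** The trial's single primary endpoint depends on finding a record, and the search key is what the participant reports. The hospital should already hold the correct number at the moment of enrolment, so the plan accepts a source of linkage error that it could avoid.

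A failed link works in one direction only: a real test goes uncounted. If such losses are equal in the two arms, the risk difference shrinks in proportion and power falls. If they differ by arm, the comparison is biased. If an unlocated test is scored as not tested rather than as missing, the multiple-imputation rule in the missing data plan (15% or more missing) would not address it.

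**Working it through.** **1. The plan's own sample size.** Inputs from the Sample size section are 35% control uptake, a 10-point improvement (45%), 90% power, alpha 5% (taken as two-sided) and 503 per arm. With pooled variance under the null and no continuity correction:

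n = [1.960·√(2·0.40·0.60) + 1.2816·√(0.35·0.65 + 0.45·0.55)]² / 0.10² = (1.3579 + 0.8832)² / 0.01 = 502.3, rounded up to 503 per arm, 1006 in total.

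The stated figure is reproduced exactly. It leaves no margin for tests that cannot be verified.

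**2. When a real test is lost.** The routes compare as follows.

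| Route | Where stated | What it needs |
|---|---|---|
| Administrative lookup | Confidentiality, Outcomes | Self-reported ID and demographics; no participant action after enrolment if both are held |
| Photo of the official record | Outcomes | Participant must send it |
| Phone and socio-demographic check | Monitoring | A test report already in hand |
| Self-report in the follow-up survey | Table 1 | Survey returned; does not count towards the primary outcome |

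A test goes uncounted only if the ID is wrong or missing, the demographic match also fails, and no photo is supplied. In participants lost to follow-up, the photo and survey routes are the ones likely to be absent. The lookup then stands alone, and a bad ID weakens it.

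**3. Effect of equal net misses.** The documents give no mis-link rate, so the range is an assumption. Let m be the share of real tests still missed after all routes, equal in both arms, with no false positives. Observed uptake is then p₁ = 0.35(1−m) and p₂ = 0.45(1−m), and with p̄ = (p₁+p₂)/2

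power = Φ{[(p₂−p₁)·√503 − 1.960·√(2p̄(1−p̄))] / √(p₁(1−p₁) + p₂(1−p₂))}.

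For m = 0.10: p₁ = 0.315, p₂ = 0.405, p̄ = 0.36. The numerator is 0.09·22.428 − 1.960·√0.4608 = 2.0185 − 1.3305 = 0.6880. The denominator is √0.45675 = 0.6758. The ratio is 1.018, and Φ = 0.846.

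| m (assumed) | Observed uptake | Risk difference | Power at 503 per arm | Total N for 90% power |
|---|---|---|---|---|
| 0 | 35.0% v 45.0% | 10.0 points | 90.0% | 1006 |
| 5% | 33.25% v 42.75% | 9.5 points | 87.5% | 1094 |
| 10% | 31.5% v 40.5% | 9.0 points | 84.6% | 1192 |
| 15% | 29.75% v 38.25% | 8.5 points | 81.3% | 1302 |

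The risk ratio stays at 0.45/0.35 = 1.286 throughout. For scale, the design expects 503·0.35 + 503·0.45 = 402.4 tested participants, so m of 5%, 10% and 15% means about 20, 40 and 60 lost tests.

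**The case against.** The strongest reply is that the ID is only one of several keys. Demographics are part of the stated tracing key, a photo needs no registration number, and test reports are checked against the phone number and baseline details. Reimbursement gives tested participants in both arms a reason to supply records. Self-reported but unconfirmed tests are a secondary outcome, so some leakage will be visible. All of this stands, and it makes the problem smaller. It does not remove it: demographics are self-reported too, the photo and the reimbursement depend on the participant, and the unconfirmed count covers only those who return the survey.

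Three stronger readings are tempting, and the documents do not support them.

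- **That any bad ID is scored as no test.** The other routes contradict this; a bad ID can lead to a missed test but need not.
- **That participants can enrol without giving an ID.** The eligibility section names contact requirements and is not a list of data fields. The Confidentiality section implies that the ID is collected, and a condensed article may leave the details to the full protocol. Likewise, the clinic rooms and endoscopy suite are called the primary sites, so recruitment of everyone at a hospital visit is a fair inference rather than a stated fact.
- **That the comparison is biased in favour of the intervention.** One could argue that intervention participants, with two weeks of messages, have more chances to correct an ID or send a photo. If controls' tests were missed 5 or 10 percentage points more often with 35% true uptake in both arms, the false difference would be 1.75 or 3.5 points and the type I error 9.0% or 21.8%. Those rates are invented for illustration. No passage describes IDs being corrected through intervention messages. Both arms add the study account, receive the final-week reminder and survey, and have their surveys checked. The trial is unblinded, so unequal loss is possible, but it is not shown.

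**Conclusion.** The point holds as an avoidable weakness in ascertainment. The protocol states a tracing method for its sole primary endpoint that relies on participant-reported identifiers, when a better source should be at hand at recruitment. No figure in the protocol is wrong because of it, and 1006 reproduces.

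The size cannot be fixed from the documents. On the assumed range of 5% to 15% net misses, equal by arm, power falls to between 87.5% and 81.3%. This is a loss of sensitivity that does not overturn the design. The result rests on the planned 35% and 45%, on no false positives, and on misses counted after every route has been tried. The change is worth making because it is cheap and protects the outcome in the participants whom the other routes are least likely to reach.

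**What to change.** - **At enrolment**, before allocation and identically in both arms, copy the HKU-SZH registration number from the visit record into the tracking log.
- **In the Confidentiality section**, state that this number is used to search HKU-SZH records for all participants, whether or not they return the follow-up survey.
- **Keep demographic matching and photo verification as active routes**, in particular for tests at other Shenzhen facilities. These count towards the primary outcome, and nothing in the protocol shows that an HKU-SZH number identifies a patient there.
- **Report by arm** the number of self-reported tests that records do not confirm, so that unequal confirmation among survey responders can be seen.

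The cost is one extra field at enrolment, which the consent must cover. Tracing of records is already planned, and no visit or procedure is added.
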